#### Exclusion criteria

Patients with estimated glomerular filtration rate < 15 ml/min/1.73 m^2^, any organ transplant, age < 19 years, pregnant women, ejection fraction < 40%, body mass index (BMI) > 30 kg/m^2^, emergency procedure, and any condition that would impede visualization of the kidneys by U/S will be excluded. Also, participants refusing to continue participating in the trial at any time during the conduction of the trial will be excluded.

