### Sample size calculation

Based on our prior experience and literature search of a 40% incidence of pAKI in this population encompassing both open and endovascular approaches of descending aortic aneurysm repairs [1, 18, 19], we expect 40% patients to develop pAKI and 60% of patients to not develop pAKI. We project that more than 70% of patients with a positive BSI to develop pAKI, while only 30% of those with a negative BSI to actually develop pAKI. From this assumption, if we recruit 80 patients to the study, we will have 32 patients expected to have pAKI (positive BSI) and 48 patients expected not to have pAKI (negative BSI). Using Fisher’s Exact Test with a 5% two-sided significance level, we will have minimum 90% power to detect the difference between 69% pAKI in patient group who will eventually develop pAKI (positive BSI) and 30% pAKI in patients who will not eventually develop pAKI (negative BSI), when sample sizes are 32 and 48, respectively. In addition, we will recruit 15 healthy group of participants to explore the feasibility of the SWE protocol, and to establish reference values on a sample of our population in terms of renal cortical stiffness, and renal parenchymal and vascular indices.

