#### Shear wave elastography exam

The ultrasonographic examination of the kidney will be performed using the Mindray Rosana 7 system (Mindray North America, CA, USA) equipped by the SC6-1u transducer for acquiring grayscale, spectral Doppler, and virtual touch tissue quantification on acoustic radiation force impulse (ARFI) imaging in the healthy adults. The exam will be performed by a certified radiology technician with over 10 years of experience and read by an independent radiologist who is blinded to the study protocol. We will use the SWE published and outlined by Sandhu et al. [20] as follows: During each encounter, both kidneys will be evaluated. The flank approach will be used to access both kidneys to minimize dissipation of U/S waves by distances traveled through or by pathology of the spleen and liver for the left and right kidneys, respectively. Exams will be performed in the left and right lateral decubitus positions for imaging the left and right kidney, respectively. Before scanning, we will adjust the image acquisition settings as follows: MI 1.4, image depth 10–12 cm, scanning frequency 3.5 MHz, single focus, dynamic range 65, harmonic imaging, Map E/Space-time 2, and total gain 0–1. The presence or absence of hydronephrosis, calculi, masses, and perinephric collections will be also assessed; the presence of any of these findings and will serve as exclusion criteria. For each participant, the following values will be obtained during suspended respiration: each kidney size in the longitudinal plane; main renal artery peak systolic velocity (PSV), end diastolic velocity (EDV), and resistive index (RI); inferior interlobular artery PSV, EDV, and RI; mid-interlobular artery PSV, EDV, and RI; superior interlobular artery PSV, EDV, and RI; shear-wave velocity values at the renal cortex (five measurements in the longitudinal plane at the upper, upper-mid, mid, mid-lower, and lower poles and three measurements in the transverse plane at upper, mid, and lower poles). All measurements will be repeated to yield two measurements per parameter per observer. Each patient will be scanned by a technician and by the principle investigator (AZ) on the study. Images will be interpreted independently by a radiologist and a vascular surgeon who are blind to the study protocol.

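### Withdrawal at any time, and ultrasound exclusions not limited to the baseline scan, can remove enrolled patients on post-operative events and bias the accuracy estimates in either direction

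*Protocol article*

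**What the plan says.** - **Exclusion criteria.** Most items are patient characteristics known before surgery, such as kidney function, age, BMI and ejection fraction. The section then adds that "participants refusing to continue participating in the trial at any time during the conduction of the trial will be excluded".
- **Shear wave elastography exam.** The scan procedure opens with "During each encounter, both kidneys will be evaluated". Within that procedure the examiner looks for perinephric collections, masses, calculi or hydronephrosis, and "the presence of any of these findings and will serve as exclusion criteria". No visit is named for this rule.
- **Procedures.** The index is measured before surgery and at 6 and 24 hours after it, so two of the three encounters are post-operative.
- **Sample size calculation.** The premise is "if we recruit 80 patients to the study". The test is Fisher's exact test "with a 5% two-sided significance level". The claim is "we will have minimum 90% power to detect the difference between 69% pAKI" among BSI-positive patients and 30% among BSI-negative patients, "when sample sizes are 32 and 48, respectively". The two groups add up to all 80 recruits, and no allowance for loss is shown.
- **Statistical analyses.** The main results are sensitivity, specificity and ROC areas for the index and its components against post-operative AKI.

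**The concern.** A diagnostic accuracy estimate is meant to describe the patients in whom the index would be used, here those having elective aortic repair. Removing patients because of something that happens after enrolment changes that population.

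A new collection around the kidney, or new obstruction, at 6 or 24 hours is plausibly linked to AKI. It may also affect the stiffness measurement, which is one of the three components of the index. A patient who stops after a complicated operation may likewise differ in AKI risk. If such patients drop out of the analysis, the analysed set is partly chosen on the pathway between the index and the outcome. Sensitivity, specificity and AUC would then describe completers with clean scans.

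The same exclusions would also reduce the number analysed below the 80 on which the power statement is based.

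**Working it through.** **Step 1: when each rule can act**

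| Rule | Section | Can it act after surgery? |
|---|---|---|
| Refusal to continue | Exclusion criteria | Yes. It acts only on people already enrolled, and at any time. |
| Hydronephrosis, calculi, masses, collections | Shear wave elastography exam | Not stated. The scan takes place at all three encounters and the rule names no visit. |
| Condition preventing ultrasound visualisation | Exclusion criteria | Not stated, but it sits among baseline characteristics. |

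The first rule needs no interpretation as to timing. The second permits two readings, screening only or any encounter, and they give different analysis sets.

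**Step 2: direction of bias (all counts assumed, for illustration)**

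Take 80 patients, of whom 40% (32) have AKI, and suppose 22 of the 32 are BSI-positive. Sensitivity is 22/32 = 68.8%. The protocol does not state this sensitivity. Its 69% is a projected AKI rate in the BSI-positive group, and 22 is chosen only to be of similar size.

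Now remove 8 patients, 6 of them with AKI. Then 72 remain, 32 − 6 = 26 with AKI, and the incidence is 26/72 = 36.1% instead of 40%. Sensitivity depends on how many of the 6 were BSI-positive:

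- 3 of 6: (22 − 3)/26 = 19/26 = 73.1%, which is higher.
- 4 of 6: (22 − 4)/26 = 18/26 = 69.2%, which is nearly unchanged.
- 6 of 6: (22 − 6)/26 = 16/26 = 61.5%, which is lower.

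The estimate rises or falls according to whether the removed AKI cases are BSI-positive less or more often than the rest. Specificity follows the same logic among patients without AKI.

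**Step 3: power**

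Inputs from the sample size section: 69% against 30%, groups of 32 and 48, two-sided 5% Fisher's exact test. Exact power is the sum, over all outcomes x and y, of Bin(x; n1, 0.69) × Bin(y; n2, 0.30), counting only outcomes with Fisher p ≤ 0.05.

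The plan's figure reproduces. Exact power at 32 and 48 is 92.8%, and the normal approximation gives 94.4%. The continuity-corrected sample size formula for 90% power returns 32 + 48 = 80.

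No loss rate is stated, so the losses below are assumptions. The 40:60 split is kept as nearly as whole numbers allow.

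| Analysed | Groups | Loss | Exact power |
|---|---|---|---|
| 80 | 32 / 48 | 0% | 92.8% |
| 76 | 30 / 46 | 5% | 90.7% |
| 75 | 30 / 45 | 6.25% | 89.97% |
| 72 | 29 / 43 | 10% | 88.6% |
| 68 | 27 / 41 | 15% | 89.0% |
| 64 | 26 / 38 | 20% | 86.5% |
| 60 | 24 / 36 | 25% | 81.3% |

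The slightly higher value at 68 than at 72 reflects the discreteness of the exact test, so differences below about one point should not be read closely. If losses come only from the smaller group, power is 91.2% after two (30 / 48) and 89.0% after four (28 / 48). The margin of about four patients therefore assumes losses roughly in proportion to group size.

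**The case against.** **The ultrasound list may be a screening rule.** No sentence says that a patient is dropped for a finding at 6 or 24 hours. Calculi and masses usually pre-date surgery. The exclusion criteria place poor visualisation beside age and BMI, and the Discussion speaks of enrolling patients without technical obstacles to ultrasound. This stands: a reader might infer a definite instruction to drop patients after surgery, but the text supports only an ambiguity. It still needs resolving, because the rule sits in a procedure repeated at every encounter.

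**Analysis sets and missing data belong to the analysis plan.** This is right as far as methods go, and their absence from a condensed article is not criticised. The point here is a rule the article does state. It is fair to add that the withdrawal sentence does not expressly say that data already collected are discarded.

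**The bias has no shown direction.** A reader might infer that accuracy would be overstated. The documents do not support that. A new collection could itself raise stiffness, and one component rising by 10% makes the index abnormal, so the patients removed could be mostly true positives. Sensitivity would then fall.

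**Withdrawals may be few.** The index needs only 24 hours of follow-up after surgery, and no loss rate is given. This also stands, and it limits the likely size of the problem.

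**Conclusion.** The concern holds as a matter of how the exclusions are defined. The withdrawal rule acts after enrolment, and the ultrasound rule is not confined to baseline. Followed literally, they can select the accuracy analysis on post-operative events. The size and direction of the resulting bias cannot be derived from the documents. With 8 assumed exclusions, 6 of them with AKI, sensitivity moves from 69% to anything between 62% and 73% across the splits shown.

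The power consequence is modest. A reader might infer that all 80 patients are needed for 90% power, but under the protocol's own test they are not. Power is 92.8% at 80 and 90.7% at 76, and first falls just below 90% at 75. It is 88.6% at an assumed 10% loss and 86.5% at 20%. These figures rest on the protocol's 69% and 30%, on a roughly unchanged 40:60 split, and on no replacement of lost patients, a matter the article does not address.

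**What to change.** 1. State that the ultrasound exclusions apply at the baseline scan only.
2. Record hydronephrosis or collections first seen at 6 or 24 hours as findings. Keep those patients in the main accuracy analysis, and add a sensitivity analysis without them.
3. Take refusal to continue out of the exclusion criteria and describe it as withdrawal. Keep data up to that point and, as consent allows, classify AKI from the hospital record. The Data collected section already gathers laboratory values and fluid balance throughout the stay.
4. State that 80 carries a margin of about four patients. If more loss is expected, restate power (about 89% at 72, 86.5% at 64) or enrol N/(1 − d). To keep 80 analysable at an assumed 10% loss, 80/0.90 = 88.9, so 89; at 20%, 80/0.80 = 100.

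The first three changes need little more than protocol wording. The cost is that some patients with poorer post-operative scans stay in, so their stiffness values may be noisier or missing. Extra enrolment is needed only if the expected loss exceeds the margin.

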### Feasibility group

A group of 15 healthy participants with no known history of diabetes mellitus (DM), hypertension or kidney, liver or heart disease and with a BMI < 30 kg/m^2^ will be enrolled. This group will serve to test the feasibility of SWE protocol and to establish reference values of normality of renal stiffness.

### Informed consent

Consent will be obtained electronically (Red Cap) via an IRB-approved consent forms by any of the research team members.

### Procedures

The bio-sonographic index (BSI) will be performed on the study patients at baseline- during their preoperative visit, and at 6 hours and at 24 hours after the procedure. The BSI will be composed of SWE, urinary cell cycle arrest (uCCA) and urinary NGAL (uNGAL). Abnormal BSI will be diagnosed as an increase of at least 10% from baseline to any of the 6 and 24 hour time points. Based on an estimated incidence of pAKI of 40% in this population, a probability of abnormal BSI will be estimated as follows (Table 1).

**Table 1 pone.0241782.t001:** The BSI criteria.

AKI	combination	SWE (YM)	uCCA	uNGAL	Patients	AKI %
Y	Abnormal	≥10% = 1, < 10% = 0	≥10% = 1 < 10% = 0	≥10% = 1 < 10% = 0	40%	90%
N	Normal	SWE <10% = 0	< 10% = 0	< 10% = 0	60%	30%

* Values are in reference to a change from baseline to any of time points 2, and 3.

AKI (Y/N) = YM based on SWE & urine biomarkers

AKI: acute kidney injury; SWE: shear wave elastography; YM; Yong Elastic Module; uCCA: urinary cell cycle arrest; uNGAL, urinary neutrophil gelatinase-associated lipocalin; Y: yes; N: no; BSI: biosonographic index; BSI score is the sum of SWE, Biomarker, and NGAL. It is abnormal if ≥ 1. Total score can range from 0 to 3.

#### Shear wave elastography exam

The ultrasonographic examination of the kidney will be performed using the Mindray Rosana 7 system (Mindray North America, CA, USA) equipped by the SC6-1u transducer for acquiring grayscale, spectral Doppler, and virtual touch tissue quantification on acoustic radiation force impulse (ARFI) imaging in the healthy adults. The exam will be performed by a certified radiology technician with over 10 years of experience and read by an independent radiologist who is blinded to the study protocol. We will use the SWE published and outlined by Sandhu et al. [20] as follows: During each encounter, both kidneys will be evaluated. The flank approach will be used to access both kidneys to minimize dissipation of U/S waves by distances traveled through or by pathology of the spleen and liver for the left and right kidneys, respectively. Exams will be performed in the left and right lateral decubitus positions for imaging the left and right kidney, respectively. Before scanning, we will adjust the image acquisition settings as follows: MI 1.4, image depth 10–12 cm, scanning frequency 3.5 MHz, single focus, dynamic range 65, harmonic imaging, Map E/Space-time 2, and total gain 0–1. The presence or absence of hydronephrosis, calculi, masses, and perinephric collections will be also assessed; the presence of any of these findings and will serve as exclusion criteria. For each participant, the following values will be obtained during suspended respiration: each kidney size in the longitudinal plane; main renal artery peak systolic velocity (PSV), end diastolic velocity (EDV), and resistive index (RI); inferior interlobular artery PSV, EDV, and RI; mid-interlobular artery PSV, EDV, and RI; superior interlobular artery PSV, EDV, and RI; shear-wave velocity values at the renal cortex (five measurements in the longitudinal plane at the upper, upper-mid, mid, mid-lower, and lower poles and three measurements in the transverse plane at upper, mid, and lower poles). All measurements will be repeated to yield two measurements per parameter per observer. Each patient will be scanned by a technician and by the principle investigator (AZ) on the study. Images will be interpreted independently by a radiologist and a vascular surgeon who are blind to the study protocol.

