### Outcome

The outcome is the development of AKI based on changes in serum creatinine and urine output according to Kidney Disease Improving Global Outcomes (KDIGO) criteria [27].

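### The image readers are masked to the study protocol, not to the clinical and biomarker information that could bias an elastography reading, and the plan does not say whose scan feeds the BSI

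*Protocol article*

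**What the plan says.** All the masking statements are in the protocol article under Shear wave elastography exam. Early in that section a technician performs the exam, and it is "read by an independent radiologist who is blinded to the study protocol". Later in the same section there are two operators, "Each patient will be scanned by a technician and by the principle investigator", and two readers: "Images will be interpreted independently by a radiologist and a vascular surgeon who are blind to the study protocol". No masking is stated for either operator. The section does not say which operator's scan, or which reader's interpretation, gives the SWE value used in the index.

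The velocities are obtained during the scan: "five measurements in the longitudinal plane at the upper, upper-mid, mid, mid-lower, and lower poles and three measurements in the transverse plane", with every measurement repeated by each observer.

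Under Procedures, the index is measured "at baseline- during their preoperative visit, and at 6 hours and at 24 hours after the procedure". The positivity rule is "Abnormal BSI will be diagnosed as an increase of at least 10% from baseline to any of the 6 and 24 hour time points", and the Table 1 footnote adds "BSI score is the sum of SWE, Biomarker, and NGAL. It is abnormal if ≥ 1".

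Under Outcome, the reference standard is KDIGO AKI: "The outcome is the development of AKI based on changes in serum creatinine and urine output".

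**The concern.** In a study of predictive accuracy, masking should keep the index-test reader from knowing anything that points to the reference standard. Here that means creatinine, urine output, KDIGO status and the other two index components. The plan states a masking target twice, and both times it is the protocol. A reader who has never seen the protocol could still know that a patient's creatinine is rising. A reader who knows the protocol well could be fully masked to everything that matters.

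The second operator adds to this. The principal investigator necessarily knows the protocol and the hypothesis, and acquires velocities. With two operators and two readers and no rule for choosing among them, the value entering the BSI is open to choice after the fact.

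At stake are the sensitivity, specificity and AUC planned under Statistical analyses for SWE alone and in combination. If knowledge of evolving AKI nudges readings upward in the patients who develop it, part of the apparent accuracy is an artefact, and no later analysis can separate it out.

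**Working it through.** **The plan's own figure.** The masking rule has no number attached. The only related figure is the power statement under Sample size calculation: 69% against 30%, groups of 32 and 48, two-sided 5% Fisher's exact test, at least 90% power. Exact enumeration gives 92.8%, so that figure reproduces. Masking would not change it. The issue is bias, not power.

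**What the stated rule hides**

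| Information | Could it bias an SWE reading? | Hidden by the stated rule? |
|---|---|---|
| Study protocol | Indirectly, through the hypothesis | Yes for readers; impossible for the principal investigator |
| Creatinine, urine output, KDIGO status | Yes, differently by AKI status | Not stated |
| uCCA and uNGAL results | Yes, and it would tie the components together | Not stated |
| Time point (baseline, 6 h, 24 h) | Yes, but alike in AKI and non-AKI patients | Not stated |

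**Illustration of size.** From the document: threshold 10%, either of two postoperative time points. Assumed, because the document gives neither: percent change in SWE is normal with mean 0 (no true effect) and SD 10, 15 or 20%. A bias b = 5% is applied in AKI patients at 24 h only, since evolving AKI is less likely to be known at 6 h.

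Single time point: P = 1 − Φ((10 − b)/SD).

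- SD 10: 1 − Φ(1.00) = 15.9%, rising to 1 − Φ(0.50) = 30.9%
- SD 15: 1 − Φ(0.667) = 25.2%, rising to 1 − Φ(0.333) = 36.9%
- SD 20: 1 − Φ(0.50) = 30.9%, rising to 1 − Φ(0.25) = 40.1%

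Either time point, changes independent: without bias 1 − Φ(10/SD)²; with bias at 24 h only 1 − Φ(10/SD) × Φ((10 − b)/SD).

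| SD | No bias | Bias at 24 h | Increase (points) |
|---|---|---|---|
| 10 | 1 − 0.841² = 29.2% | 1 − 0.841 × 0.691 = 41.8% | 12.6 |
| 15 | 1 − 0.748² = 44.1% | 1 − 0.748 × 0.631 = 52.9% | 8.7 |
| 20 | 1 − 0.691² = 52.2% | 1 − 0.691 × 0.599 = 58.6% | 6.4 |

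The two changes share one baseline, so they are correlated. With correlation 0.5 (bivariate normal in place of the product):

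- SD 10: 25.5% to 37.0%, +11.5 points
- SD 15: 38.3% to 46.3%, +8.0 points
- SD 20: 45.4% to 51.3%, +5.9 points

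**Sensitivity to b.** With independent changes, the increase is Φ(10/SD) × [Φ(10/SD) − Φ((10 − b)/SD)].

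- b = 2%: 0.841 × (0.841 − 0.788) = 4.5 points at SD 10; 0.691 × (0.691 − 0.655) = 2.5 points at SD 20
- b = 10%: 0.841 × (0.841 − 0.500) = 28.7 points at SD 10; 0.691 × (0.691 − 0.500) = 13.2 points at SD 20

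**Carry-over to the BSI.** These increases are in the SWE component. A biased SWE reading changes the BSI classification only in patients with neither urinary marker positive. If that share is u, and SWE is independent of the urinary markers, the BSI-positive rate rises by u times the SWE increase. The document gives no u. At u = 0.5, 6.4 to 12.6 points become 3.2 to 6.3.

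**Time point alone.** With no true effect, the same upward shift in all postoperative scans raises the positive rate equally in AKI and non-AKI patients. Sensitivity goes up, specificity goes down by the same amount, and their sum does not change.

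**The case against.** The case on the other side has several sound parts.

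- *The document does not say that anyone is influenced.* A reader might infer that the vascular surgeon treats these patients, or that the principal investigator scans with the results in view. Neither is stated. The radiologist is called independent, and the surgeon is not identified as the treating one. That the principal investigator is unmasked is an inference from the role and from the absence of any stated masking.
- *AKI may not be known at the scan.* A reader might infer that creatinine and urine output are in hand before the 24 h exam. Table 3 lists daily monitoring but places no result before that exam, and the Discussion notes that kidney decline presents late after endovascular repair. The exposure is therefore mainly early-onset cases at 24 h, or stored images read later; when images are read is not stated.
- *There are safeguards.* Machine settings and cortical sites are fixed, measurements are repeated, velocity is a measured quantity, and the planned observer analysis could show a difference between operators.
- *An article condenses.* Image handling and reading order may well sit in the full protocol.

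The first two points limit how strongly the concern can be put, and the third lowers the likely size of bias. The fourth does not dispose of it: the article does not leave the masking target open. It states one twice, and that target does not cover the information that could bias a reading. An operator comparison also cannot show a bias shared by both operators.

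**Conclusion.** The concern holds as a misdirected masking rule and an undefined source for the SWE value. It is not a demonstrated bias. The stated target leaves readers free to know creatinine, urine output, biomarker results, KDIGO status and time point, while a 10% change in SWE alone can turn the BSI abnormal.

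Under the stated assumptions (no true effect, b = 5% at 24 h in AKI patients only, SD 10 to 20%), the spurious gain in the SWE-positive rate is about 6 to 13 points with independent changes and about 6 to 11 with correlation 0.5. It is no more than that for the BSI as a whole. Both the bias and the SD are assumed, so these figures show scale and are not estimates.

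Two stronger readings are not supported. One is that the gain could reach 23 points (29% to 52% at SD 10). That applies the known-AKI bias at 6 h as well and treats the two changes as independent. The other is that knowing the time point in itself biases results toward the outcome. It mainly trades specificity for sensitivity. The outcome rests on laboratory and urine-output criteria, and no defect is shown in how it is ascertained.

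The change should be made before images are read.

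**What to change.** Under Shear wave elastography exam:

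1. Replace both statements of masking to the protocol with: *Readers are blind to serum creatinine, urine output, biomarker results and KDIGO status. Images are stripped of patient identity, date, time point and operator and are read in random order.*
2. Reconcile the two descriptions of who scans and who reads. State that the SWE value in the BSI comes from the technician's scan, and that the principal investigator's scan is used only for the inter-observer analysis. State also which reader's interpretation counts, or how the two are combined.
3. Keep biomarker results and KDIGO status from both operators where practicable. Bedside operators cannot be masked to time point, and masking them to urine output may not be feasible in intensive care.

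The cost is wording, image de-identification and a shuffled reading list, with no extra patients, scans or readers. Reads become batched rather than live. Because velocities are obtained during the scan, masked reading does not fully remove bias arising at acquisition. The article should say so as a limitation.
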